### Recording and reliability

All assessment and treatment sessions will be audio-recorded using a Sony ICD-UX71F recorder, and video-recorded with a Cinde 88 audio-visual-system. The first two authors will supervise speech pathology clinicians using the in-house closed circuit video system to observe sessions from a different room in real-time with minimal distraction for the children. Professional recorders (Echo Layla 24/96 multitrack recording system, Marantz PMD660 solid-state recorder and a Roland Quad-Capture UA-55) will be used for high-quality audio-recording of children’s speech for all experimental probes and assessments. Recordings will use 16Bit and 48,000 Hz sampling rate to allow for future acoustic analysis, if warranted.

## Discussion

### Potential significance

This will be the first randomised control trial to test any treatment for CAS [14]. It is predicted that this will be valuable for clinical decision making and ultimately for providing evidence-based and timely services for children with CAS which may improve access to services and reduce the burden of the disorder. Potentially both treatments will be shown efficacious to some degree or for specific behaviours, which offers two evidence-based options tested at a gold standard level. If the treatments are successful, further work in ensuring time-efficient translation into practice can be pursued in effectiveness studies, knowing the treatments are efficacious and such work is warranted. Examples of this may include computer-based delivery of treatment to promote home practice and achieve treatment intensity with fewer face-to-face clinician-directed sessions.

As both treatments also vary in their application of Principles of Motor Learning, future investigations of the treatments may explore the effects of these differences on long-term outcomes. Recently Maas and colleagues [13] used DTTC with varied frequency feedback in treatment – low frequency (feedback on 60% of trials) and high frequency (feedback on 100% of trials). Two participants responded more favourably to low frequency feedback yet another responded more favourably to high frequency feedback, and regardless of feedback frequency generalisation was limited. Due to a sample size of three, it is unclear why these patterns may have occurred. Additionally Maas and colleagues [65] explored blocked versus random practice in terms of long-term maintenance and transfer. Again the results were mixed with two participants favouring blocked practice, another performing better with random practice and the fourth participant responding to neither condition. Our research will not explicitly test these motor learning principles, as we are using the treatments as faithfully as possible to their original form. However, the two treatment approaches differ in their application of key principles: the NDP3 uses high frequency feedback while ReST uses high frequency feedback in Pre-Practice and low frequency feedback in practice; the NDP3 uses blocked practice on specific speech targets but random presentation of words within blocks while ReST uses random practice in the Practice component. It will therefore be interesting to analyse the results for each treatment considering the inherent Principles of Motor Learning utilised.

### Potential limitations

As this is a behavioural treatment, it is not possible to blind clinicians and participants to treatments as per CONSORT [66] and PEDro guidelines [67]. Even though parents will not be told the name or details of the treatment their child will receive until their participation has ended, they could still talk to another parent in the waiting room and realise the treatments are different.

Clinicians will conduct all treatment sessions with two assigned participants using the ReST treatment for one and the NDP3 treatment for the other. Thus they will be required to be trained in and deliver both treatments. This is to reduce potential clinician effects. There is potential for drift across methods, motivating supervision of sessions by the authors and calculation of treatment fidelity on a portion of all treatment sessions.

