## Methods and design

A parallel group, fixed size randomised control trial will be conducted in Sydney, Australia to determine the comparative efficacy of two treatments for Childhood Apraxia of Speech: the Rapid Syllable Transition Treatment (ReST) and the Nuffield Dyspraxia Programme – Third edition (NDP3). This protocol has been approved by the Human Research Ethics Committee of the University of Sydney (approval number 12924).

A power calculation has been used to determine the number of participants to be recruited. Previous pre and post treatment data from within-subject ReST studies (e.g. [12,16]) for a total number of 14 participants demonstrated statistically significant differences for 12 of the 14 participants and large effect sizes (Cohen’s d = 1.36). Based on this, the estimated sample size to detect a reliable treatment effect (alpha level 0.05, beta level 80%) is 6 per group for this RCT. We have no estimates for the NDP3 due to lack of published effect sizes or data to enable calculation of an effect size. On this basis we propose 10 per group to allow for attrition and to accommodate the higher heterogeneity with a between-subjects design.

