### Intervention delivery and dosage

The two treatments will be conducted in parallel within three treatment blocks over school holiday time in Sydney, Australia, permitting a maximum of 10 participants per block to allow for recruitment of between 20 and 30 participants across 3 treatment blocks. Treatments will be delivered by trained and supervised speech pathology clinicians. Each child will be allocated one clinician for all treatment sessions. Clinicians will be blinded to hypotheses. The parents of children will not be informed of the name and strategies of the treatment their children are receiving until after data collection is completed to ensure no home practice will be attempted.

All participants, regardless of treatment condition, will receive the same amount of time in treatment with 1-hour sessions, four times a week for three weeks for a total of 12 treatment hours. All participants will complete between 100–120 production trials on treatment words per 1-hour session (i.e. a total of 1200 to 1440 responses during treatment), to match the practice intensity and session distribution of our pilot studies of ReST [12,16] and the current best evidence of treatment intensity for CAS [61]. For the NDP3 programme this will equate to approximately 30–40 trials during each 18 minute period for each goal. For the ReST programme, this will equate to 5–20 Pre-Practice trials and 100 practice trials.

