#### Data analysis

Clinical effect sizes will be reported using Cohen’s d. A series of repeated measures ANOVA with between subject factor of treatment (NDP3, ReST) and within subject factor of time (pre-, 1 week post-, 1 month post-, and 4 months post-treatment) will be used to determine the relative efficacy of the two treatments as measured by the 292-item experimental probe. Separate analyses will be run for treated stimuli, to document treatment and maintenance effects, and untreated stimuli, to document generalisation of treatment effects and their maintenance. Additional repeated measures ANOVA (2 groups x 4 time points) will be run for the DEAP Inconsistency subtest [49], GFTA-2 [58] and the Test of Polysyllables [50,51]. If there is any attrition, an intention-to-treat analysis will be conducted.

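### Each clinician treats one child per arm, but the planned ANOVA has no clinician term, so the between-arm test is miscalibrated if clinicians differ in the gains they produce

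*Protocol article*

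**What the plan says.** Three sections of the protocol article bear on this.

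- **Intervention delivery and dosage:** "Each child will be allocated one clinician for all treatment sessions".
- **Potential limitations:** "Clinicians will conduct all treatment sessions with two assigned participants using the ReST treatment for one and the NDP3 treatment for the other". The reason given is "This is to reduce potential clinician effects". The same paragraph accepts a risk of drift between methods as the price.
- **Data analysis:** the probe is to be analysed by "repeated measures ANOVA with between subject factor of treatment (NDP3, ReST) and within subject factor of time", in separate runs for treated and untreated stimuli. No clinician or pair factor is named.

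Two other sections set the context. Group allocation randomises individual children by numbered envelopes and does not mention clinician or treatment block. Methods and design gives the size: "we propose 10 per group to allow for attrition and to accommodate the higher heterogeneity with a between-subjects design".

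**The concern.** Two children treated by the same clinician for 12 sessions may gain more, or less, than average together. Where that happens, the shared part cancels from the ReST minus NDP3 difference, because every clinician contributes one child to each arm. The planned ANOVA treats all children as independent, so it leaves that shared variance in the error term.

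The resulting standard error is too large, the confidence interval too wide, and the test runs below its stated 5%. This matters in a trial of 10 per group whose second and third hypotheses predict that ReST will be superior. It matters differently for the first hypothesis, which predicts similar gains at 1 week. If a non-significant difference were read as similarity, a test running below its nominal level would make that conclusion easier to reach.

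**Working it through.** **Inputs.** From the documents: one child per arm per clinician, 10 per group planned, and up to 30 children in total. Two children per clinician gives 20/2 = 10 or 30/2 = 15 clinicians, if none is used twice. Alpha is 0.05 and d = 1.36. Assumed: the clinician ICC of the gains, for which no value is given; the range is 0 to 0.5. Also assumed, as a less optimistic effect: d = 1.0.

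**The plan's own figure.** The protocol says "the estimated sample size to detect a reliable treatment effect (alpha level 0.05, beta level 80%) is 6 per group for this RCT". With d = 1.36 and 80% power, a within-subject calculation gives ((1.960 + 0.842)/1.36)² = 4.2, so 5, or 7 by exact paired t. A two-sided two-sample calculation gives 2 × 4.2 = 8.5, so 9, or 10 by exact t. The stated 6 lies in the within-subject range. At the planned 10 per group, a two-sided two-sample t-test has 82% power at d = 1.36. Neither calculation involves clinicians.

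**Standard error.** Take total variance σ² per child, share ICC due to clinician, and n pairs.

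- Planned (children independent): variance of the arm difference = 2σ²/n.
- Actual (crossed): variance = 2σ²(1 − ICC)/n.
- Ratio of standard errors = 1/sqrt(1 − ICC): 1.054, 1.118 and 1.195 at ICC 0.1, 0.2 and 0.3.

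**Type I error and power.** Simulation of one between-arm contrast (for example, change from baseline), 100,000 runs per setting, unpaired against paired t-test, two-sided 5%:

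| Pairs | ICC | Type I error, unpaired | Power at d = 1.0, unpaired / paired |
|---|---|---|---|
| 10 | 0 | 5.0% | 56% / 51% |
| 10 | 0.1 | 3.9% | 56% / 56% |
| 10 | 0.2 | 3.2% | 57% / 61% |
| 10 | 0.3 | 2.2% | 57% / 66% |
| 15 | 0 | 4.9% | 75% / 72% |
| 15 | 0.1 | 3.9% | 76% / 77% |
| 15 | 0.2 | 3.0% | 78% / 81% |
| 15 | 0.3 | 2.1% | 79% / 86% |

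**Break-even for strict pairing.** Pairing cuts the error degrees of freedom from 18 to 9 (10 pairs) or from 28 to 14 (15 pairs). Interval widths are equal when ICC = 1 − (t_unpaired/t_paired)².

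- 10 pairs: 1 − (2.101/2.262)² = 0.14.
- 15 pairs: 1 − (2.048/2.145)² = 0.09.

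**Which clinician term is needed.** Write a child's score at time t as a clinician intercept plus other terms. In the change from baseline, the intercept appears in both scores and drops out. Fits to balanced simulated data (10 pairs, four times) confirm this: the treatment × time standard error was the same with and without the intercept (0.2713 and 0.2713 in one data set, 0.2964 and 0.2964 in another). Only a clinician effect on the gains changes it.

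**Random clinician effect on gains, tested on n − 1 degrees of freedom.** At 10 pairs and d = 1.0, power against the unpaired test is 56% vs 56% at ICC 0 and 63% vs 57% at ICC 0.2. Type I error is highest at ICC 0, about 5.7%. If the term is dropped whenever its estimated variance is not positive, and the test reverts to 18 degrees of freedom, type I error at ICC 0 is about 6.4%.

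**The case against.** The strongest reply has four parts.

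1. **The design purpose is met without modelling.** Having each clinician deliver both treatments removes clinician confounding from the arm contrast whatever the model. This stands. A reader might infer that the plan biases the comparison, or analyses the data as though the crossing had not been done; the documents do not support that.
2. **The error is on the cautious side.** This also stands: no inflated false-positive rate follows from the omission. But an interval that is too wide and a 5% test that runs at 3% are still miscalibrated.
3. **The ICC is unknown and may be small.** Manuals, supervision and an 85% fidelity benchmark all work against large clinician differences. It is tempting to say that the precision bought by the design is thrown away. That cannot be claimed: below an ICC of about 0.14 at 10 pairs, strict pairing loses power (79.3% vs 82.5% at ICC 0.05 and d = 1.36).
4. **The pairs are not built into randomisation.** A reader might take the children to be matched pairs sharing a clinician and a holiday block. Group allocation describes neither. Assuming 15 envelopes per arm (not stated) and full blocks of 10, the chance of a 5:5 split in a given block is C(15,5)²/C(30,10) = 30%. This stands, and it argues against a compulsory paired test, though not against a clinician term.

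It could also be said that a clinician term belongs in an analysis plan that is not shown. The point here, however, concerns the factors that the article itself fixes.

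**Conclusion.** The concern holds as a matter of calibration and possible loss of precision. The stated model does not match the stated design whenever clinicians differ in the gains they produce. The standard error is then overstated by 5%, 12% or 20% at ICCs of 0.1, 0.2 or 0.3, and type I error with 10 pairs falls to about 4%, 3% or 2%.

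These figures rest on an assumed ICC, on complete one-per-arm pairs, and on a single between-arm contrast; the full 2 × 4 interaction was not simulated. If the ICC is zero, the planned analysis is correctly calibrated. The change is worth making because it is cheap and because adding clinician after the data are seen would be a post hoc choice.

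**What to change.** In Data analysis, state that clinician enters as a random effect on post-treatment response. Either of these will do:

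- model follow-up scores adjusted for baseline, or change scores, with a random clinician effect; or
- keep all four time points and add a random clinician × time term.

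A clinician intercept alone should not be used as the remedy. State that the term stays in the model whatever its estimated variance, and name in advance a small-sample degrees-of-freedom method based on the number of clinicians. Use a mixed model and not a mandatory paired test, so that a child whose clinician lacks a counterpart in the other arm still contributes.

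**Cost.** A sentence or two of text and one extra variance component; each child has one clinician throughout, so clinician identity is available. If clinicians do not differ, a strict paired analysis would lose about 5 points of power at 10 pairs and 3 at 15 (d = 1.0). The random effect loses essentially none, but its type I error can reach about 5.7%.

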## Abbreviations

CAS, Childhood Apraxia of Speech; NDP3, Nuffield Dyspraxia Programme – Third edition; ReST, Rapid Syllable Transition Treatment; DTTC, Dynamic Temporal and Tactile Cueing; CELF, Clinical Evaluation of Language Fundamentals; GFTA-2, Goldman Fristoe test of Articulation - Second edition; KP, Knowledge of Performance feedback; KR, Knowledge of Results feedback.
